##### Health related quality of life

To measure health related quality of life, the adapted and validated German version of the Veterans RAND 12-Item Health Survey (VR-12) will be used [77]. The four-week retrospective questionnaire can be summarized into two parent scales (1) Physical Component Scale and (2) Mental Component Scale each derived from four different health domains ((1): physical functioning, role physical, bodily pain, general health), ((2): (vitality, social functioning, role-emotional, mental health). The question on general health is further used as an one-item instrument for patient global assessment [41].

##### Overall perceived benefit

The overall satisfaction with the perceived results of the intervention will be evaluated using a one item question with a 5-point Likert scale according to Rolfson, Wissig [42].

##### Disease specific outcomes

To assess the status of knee and hip OA, the German versions of the Knee Injury and Osteoarthritis Outcome Score (KOOS) [78] and Hip Dysfunction and Osteoarthritis Outcome Score (HOOS) [79] will be applied to the participants with knee and/or hip OA. Both questionnaires consist of 5 subscales: pain, symptoms, activity of daily living, function in sport and recreation and knee or hip related quality of life. The disease-specific instruments are valid, reliable, easy to complete and simple to score [79, 80]. In addition, the participants will be asked to rate their pain during the last four weeks on a visual analog pain scale.

The Prospective Cardiovascular Münster (PROCAM)-Score is a simple and effective way to assess the risk of acute coronary events among adults [81]. Participants with a 10-year myocardial infarct risk > 10% when compared to the reference group are listed as participants at risk for CVD. For the study, the shorter version of the questionnaire will be used which includes: age, weight, height, systolic blood pressure, gender, smoking status, family disposition, current drug treatment of hypertension, DMT2 status [82].

To assess the risk for developing DMT2 within five years, the German Diabetes Risk Score (GDRS) will be used [30, 31]. This noninvasive measurement showed an excellent discrimination in detecting prevalent undiagnosed DMT2. A score of  ≥ 57 points indicates an increased risk of developing diabetes in the next 5 years.

##### Dietary intake

The food frequency questionnaire (FFQ) details the frequency and portion size of common consumed foods. In total, 29 food groups are assessed. The FFQ used in this study was developed for the German Health Examination Survey for adults 2008–2011 (DEGS) [44]. For the German adult population it shows reasonable validity [44].

##### Physiological outcomes

Spiroergometry will be performed to determine the maximum oxygen (O_2max_) uptake, the respiratory ratio and physical working capacity. Therefore, bicycle ergometry will be conducted (incremental test until exhaustion, duration of each increment: 2 min, start at: 0,5 watts x body weight in kg, increment: 0,3 watts x body weight in kg). The breathing gas analysis is carried out using Aeroman professional (Aeroscan GmbH, Berlin). For this purpose, the participant breathes through a breathing unit for 30 s at the end of each stage. A 12-channel resting ECG (custo cardio 300, custo software, custo med GmbH) after 5 min rest will be performed before the performance test to rule out abnormalities and to assess resting blood pressure. Also, during the entire test, an ECG will be recorded and supervised by a physician at t0. Reasons for immediately stopping the ergometry include chest pain, systolic blood pressure > 200 mmHg, ECG abnormalities, intolerable dyspnea and cramps. In addition, capillary blood will be dropped onto a Guthrie-card during performance diagnostics (before and after exercise) for all participants. These serve to record various metabolic markers.

Lower body strength and leg strength endurance will be measured with the 30-Second-Chair-Stand Test. For the test, the participant sits in the middle of a chair, hands clasped in front of the body, feet flat on the floor and back straight. The test person will be asked to stand up, in a completely upright body position, and to sit down on the chair again as many times as possible within 30 s. Depending on gender and age, the minimum number of repetitions will be graded [45].

Body composition will be assessed with bioimpedance analysis (BIA 101 BIVA, SMT medical GmBH & Co). In a lying position, two skin electrodes will be attached to the hands and feet on one side of the body and connected to the BIA101 BIVA via a thin measuring cable. The measured values appear on the device display and will be transferred wirelessly via Bluetooth to the Bodygram PLUS software.

For a predefined sub-sample only (*n* = 20 IG, *n* = 20 CG), laboratory parameters (urine, blood) will be assessed. Subgroup laboratory data analysis include standard laboratory data, adipokines and osteoarthritis markers, metabolomics and qPCR analysis of miRNAs. Trained staff will collect venous blood in the morning after 12 h fasting. Selected miRNAs as well as various markers for osteoarthritic events (COMP, CTXII) and for metabolic function (leptin, adiponectin, resistin) will be recorded in blood or urine samples. Finally, laboratory parameters that are usually positively influenced by physical training (fasting blood glucose, Hba1c, insulin, IL-6, CRP, cholesterol, LDL and HDL) will be analyzed. Approx. 40 ml of blood will be taken at each of the measurements.

*Exercise psychological outcomes* Exercise-specific self-efficacy will be measured with a questionnaire based on the validated Multidimensional Self-Efficacy for Exercise Scale (MSES) [46], which has already been applied in other exercise studies [83]. The MSES comprises nine Likert-like items assessing the three behavioral subdomains task, coping, and scheduling efficacy on 100% confidence scales.

To capture the concept of sport and exercise-related self-concordance, a German-language instrument for measuring the self-concordance of sport- and exercise-related goals (SSK-Scale) will be applied [47]. The validated 12-item version of the scale captures four 3-item subscales measuring the intrinsic, identified, introjected, and extrinsic modes of motivation on a 6-point Likert scale [47].

According to the model of physical activity-related health competence (PAHCO), we will assess the sub-scales control competence for physical load, competence for PA-specific affect regulation, and PA-specific self-control. We will apply the validated 13-item version of the PAHCO questionnaire, which uses a 5-point Likert scale [21].

Sport and exercise specific motivational competence will be operationalized using a one-dimensional scale developed and validated by Schorno, Sudeck [49]. It measures the self-determined ability to choose a suitable exercise and sport activity. The 4-item questionnaire covers the following three facets of motivational competence on a 5-point Likert scale: knowing one’s own preferences, knowing what to expect in different exercise and sport activities, and choosing and arranging an exercise and sport activity [49].

Action and coping planning will be assessed using the validated exercise planning scales developed by Sniehotta, Schwarzer [50]. It includes four items on each of the two subdomains, action plans and coping plans, on a 4-point Likert scale.

To assess attitudes towards physical activity in its cognitive and affective components, a psychometrically tested German version of the validated questionnaire developed by Crites, Fabrigar [84] will be applied. In this short questionnaire, four items each assess the two components using semantic differentials with both positive (e.g., *healthy*) as well as negative (e.g. *useless*) adjectives included on a 7-point bipolar scale [84].

Motives and goals for exercise participation will be evaluated throughout the first intervention phase (week 7) at t6, t12 and t18 for the intervention group only, using the Bernese motive and goal inventory (BMZI) [85]. The updated version of the questionnaire consists of 23 items covering seven motives and goals (Body/Appearance, Contact, Competition/Performance, Aesthetics, Distraction/Catharsis, Fitness and Health) [86].

To assess fear of movement/(re)injury, the German Version of the Tampa Scale for Kinesiophobia (TSK-GV) will be applied [53]. The 11-item version of the TSK-GV with a 4-point Likert scale has been shown to be a reliable and valid measure. Results of the scale may be predictors for the persistence of pain-related disability [53].

##### Economic data (insurance data base; firm software)

Economic data comprise unspecific and specific disease related health care costs. Intervention related costs for the exercise program will be taken into consideration as well.

Unspecific health care costs (overall costs): Outpatient acute care, hospital costs, rehabilitative treatment, medically prescribed supplementary treatments (*e.g.* hydrotherapy, physiotherapy, massages), adjuvants, costs related to periods of disability, medication and intervention related costs.

Specific medical costs refer to the costs of the diagnoses CVD, DMT2, hip and/or knee OA, OW/OB and the intervention costs.

##### Process evaluation

Over the whole study period, the intervention will be evaluated from the perspective of interventionists, participants, study sites and involved organizations in the form of questionnaires, qualitative interviews (QI), documentation and notation sheets and telephone screenings.

To compare the intervention program with the characteristics of the standard care arm, the control group will be asked questions on the utilization of standard care offers.

Participants’ satisfaction with *MultiPill-Exercise* will be evaluated using a modified version of the ZUF-8 within the intervention group [54, 87]. In order to adapt the 8-item instrument (4-point Likert scale) to the outpatient setting, minor modifications were made. In addition, qualitative interviews will be conducted with participants of the intervention group after program completion, including questions on the appropriateness and quality of the intervention delivery, with the aim of gaining greater insight into participants' views on the intervention.

To assess treatment fidelity, standardized notation sheets will be used for the various intervention modules (exercise, participant education session, individual counselling sessions). Interventionists will be instructed to record any deviations concerning the intended intervention delivery. Further, the study team will document any questions of the interventionists regarding the program delivery. This kind of ‘troubleshooting’ during the intervention phases will not only ensure high treatment fidelity but also provides information on possible barriers and facilitators of the intervention delivery.

To capture characteristics of the interventionists, the following questionnaires will be used in versions adapted to *MultiPill-Exercise* before (t0) and after the intervention (t6): First, a German version of the Occupational Self-Efficacy Scale (OCCSEFF) [88] modified according to Rigotti, Schyns [55]; second, a scale transferred from the school context assessing subjective task values [56]; and third, we use items of the three implementation outcome measures according to Weiner, Lewis [89]: Acceptability of Intervention Measure (AIM), Intervention Appropriateness Measure (IAM), and Feasibility of Intervention Measure (FIM).

In-depth analyses on interventionists’ view on the program will be done based on qualitative interviews with at least seven of the interventionists after the last intervention delivery regarding acceptability, practicality, appropriateness and fidelity aspects of the latter. In addition, their satisfaction with the interventionists’ training regarding the overall structure, contents and methods will be assessed in accordance to a formative evaluation procedure regarding exercise therapist training developed by Göhner, Schagg [58].

The evaluation of implementation regarding interfaces of the health service innovation will be conducted by employees of the health insurance company (APS) with short questions based on the AIM, IAM and FIM [89] regarding the practitioners’ view on the acceptability, appropriateness and feasibility of the program and its prescription. In addition, participants in the control and intervention groups will be asked about their mode of access into the study program during telephone screenings that will take place during recruitment. The evaluation of implementation regarding the interface with community-based exercise offers will be carried out after the last intervention delivery using qualitative interviews with a sub-sample of the participants of the intervention group (14 in total) and at least seven employees of the health insurance company.

##### Adherence

The number of attended training sessions will be documented by the exercise instructors for all on-site trainings. Furthermore, the returned training logs (number and type of exercises, subjective exhaustion) will be evaluated for training adherence.

##### Safety: Adverse events and side-effects

The rating of the safety of the intervention is documented by listing exercise related adverse events or side-effects by different parties: The exercise specialists of the study sites will document all potential adverse events of the exercise of which they have become beware of. Participants are urged to report adverse events or side-effects to their guide or to report them in their training-log. Exercise-related adverse events are also retrospectively assessed via the online questionnaire at t3 and t6. All participants can further contact the study physician of the university hospital at any time as outlined in the participant information sheet. The standard adverse events and severe adverse event form of clinical trials will be implemented in the SecuTrial database.

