	**Economic Data**			
Unspecific and specific (disease-related) health care costs	Outpatient costs, hospital costs, medication, adjuvants, rehabilitation treatment, medically prescribed supplementary treatments (e.g. hydrotherapy, physiotherapy, massages)	IDB	IG, CG	tm18, tm12, tm6 t6, t12, t18
Unspecific/specific (disease related) periods of disability	Days of disability (overall and related to referred diseases)	IDB	IG, CG	tm18, tm12, tm6 t6, t12, t18
Intervention related costs	Costs for human and physical resources/session	IDB	IG	t6, t18

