	**Safety and Adverse Events**			
Adverse events and side-effects	Summarized number and details of adverse events and side-effects according to training log and case report form	Training logs, on-site CRF, SAQ	IG	t3, t6

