(2)In order to strengthen the effect and action knowledge of the participants, participant education sessions of 30 min each will be held, delivering theoretical and practical knowledge on the basics of training sciences, nutrition (healthy and anti-inflammatory diet), themes to enhance motivation and volition [63], motives and goals of PA [23, 52] and PA in daily life [64]. While five theory sessions will be scheduled for phase 1, phase 2 will include a nutritional booster session (anti-inflammatory diet). A theory–practice link is always strived for. 

(3)Three individual counselling sessions (30 min each) using further behavioral change techniques will take place in phase one. The individual counselling to enhance regular sport participation will be conducted by a guide; an exercise specialist who will also act as a personal contact person. The guide will be briefed on the diverse behavior change techniques included (MoVo-Lisa concept [65], the exercise counseling approach based on motives and goals in exercise and sport (COMET) [23], including 5A’s [66], and techniques from Motivational interviewing [67]). The personal guide will also be responsible for weekly feedback on the participant’s training logs. Phase two includes two individual counselling appointments (anti-inflammatory diet and COMET). The counselling sessions are based on the individual training diaries, the participant’s feedback on the movement teasers and the individual results of the assessment of the Bernese motive and goal inventory in exercise and sport (BMZI) [52]. The counselling on nutrition and dietetics will build on two seven-day nutrition logs (these are kept after each of the nutrition lectures) and will be evaluated and discussed with a nutritionist from the insurance company.

All individual and group sessions on-site will be conducted by exercise professionals, employees of the statutory health insurance company at each of the study sites. Several exercise specialists and nutritionists from the statutory health insurance company will be trained in advance on the *MultiPill-Exercise* intervention design. Only trained exercise professionals will also act as guides in the intervention. The exercise specialists will receive a comprehensive manual for delivering the exercise intervention to enable standardization across study sites.

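### The safety rating and its only scheduled inquiry are limited to exercise-related events as judged by unblinded participants and instructors, while Table 2 states the outcome without that limit

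*Protocol article*

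**What the plan says.** The section on adverse events and side-effects in the protocol article opens with the rule that governs the safety rating: "The rating of the safety of the intervention is documented by listing exercise related adverse events or side-effects by different parties". It then describes how events reach the study:

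- Instructors: "The exercise specialists of the study sites will document all potential adverse events of the exercise", as far as they learn of them.
- Spontaneous participant reports: "Participants are urged to report adverse events or side-effects to their guide or to report them in their training-log".
- Questionnaire: "Exercise-related adverse events are also retrospectively assessed via the online questionnaire at t3 and t6".
- Physician contact: "All participants can further contact the study physician of the university hospital at any time as outlined in the participant information sheet".
- A standard form for adverse and severe adverse events is set up in the trial database.

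Table 2 lists the safety outcome as "Adverse events and side-effects" and describes it as their number and details, with no condition on relatedness. Its sources are training logs, the on-site case report form and the self-administered questionnaire. It is collected in the intervention group at t3 and t6.

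The blinding section states that participants and exercise specialists know the allocation. On who delivers the programme, the intervention section says: "All individual and group sessions on-site will be conducted by exercise professionals, employees of the statutory health insurance company". The data availability statement adds that this insurer will adopt the programme if the study succeeds.

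**The concern.** Safety is a declared aim of the trial, named beside effectiveness and efficiency in the study design section and again in the conclusion. A restriction to exercise-related events asks someone to decide on cause before anything is written down. Here that person is a participant, or an instructor employed by the organisation that offers the programme. Neither is blinded.

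The population makes this attribution hard. Participants have at least two of osteoarthritis, diabetes risk, cardiovascular risk and overweight or obesity, and part of the training takes place at home. A joint flare or a cardiac symptom some hours after a session can easily be put down to the existing condition. An event recorded and later judged unrelated can be reviewed. An event never recorded cannot.

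The mismatch with Table 2 adds a second problem: a reader of the results could not tell which of two definitions the reported count follows.

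**Working it through.** The plan gives no figure on this point, so the check is a comparison of passages.

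**Step 1: filter by route.** The safety section names five channels.

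| Channel | Limited to exercise-related events? | How it is triggered |
|---|---|---|
| Specialists' record | Yes, though worded as *potential* events of the exercise | When the specialist becomes aware |
| Questionnaire at t3 and t6 | Yes | Scheduled |
| Guide or training log | No | Participant volunteers it |
| Contact with study physician | No | Participant initiates it |
| Standard event form | No | A place to record; the article does not say who completes it |

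Two of the five are filtered and three are not. The questionnaire is the only one described as a scheduled question put to participants, and it is filtered.

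**Step 2: what feeds the rating.** The opening sentence defines the rating itself as a list of exercise-related events. An event that arrives through an unfiltered channel still has to be judged exercise-related to enter that list. The unfiltered channels widen what may be recorded, but they do not change what is rated.

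**Step 3: two definitions, one data set.** Let A be the number of all recorded adverse events and side-effects, and R the number of those judged exercise-related. Table 2 asks for A; the safety section asks for R. R is part of A, so R ≤ A, and the two are equal only if every recorded event is judged related. The same records can thus support two different safety counts.

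**Step 4: a traced example.** Suppose that a participant has a knee flare the evening after training and blames long-standing osteoarthritis.

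- The questionnaire as described does not cover it.
- The specialist may record it, if told and if it is thought a potential event of the exercise.
- The participant may enter it in the training log, and it then counts under Table 2.
- It enters the rating in the safety section only if someone reclassifies it as exercise-related.

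It may be captured, but nothing scheduled asks for it.

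**Step 5: data that need no attribution.** The economic section of Table 2 already draws hospital and outpatient costs and "Days of disability (overall and related to referred diseases") from the insurance database for both arms at t6, t12 and t18. These do not depend on anyone's view of cause. They are planned as economic data, not as safety data.

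**The case against.** The strongest reply is that a reader might infer that every route is filtered, or that unattributed events are lost before a physician could learn of them, and that the text supports neither. This stands. Participants are asked to report events to the guide or log without a relatedness condition, anyone may contact the study physician, and a standard event form exists. The word *potential* in the instructors' task also reaches suspected events, beyond those already judged related.

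A reader might also infer that no physician ever assesses causality. The article describes no such step, but it is a condensed account. Who completes the form and who rates causality may be set out in the full protocol, so that silence is not counted here. The on-site case report form may also be supplied by a physician where applicable.

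Third, Table 2 uses short labels, and its row could be read together with the fuller text. That reading is possible, but it leaves the scope to be guessed. The table's description asks for number and details of events and carries no qualifier.

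What survives is narrower: an explicit rule limits the rating, the same limit applies to the only scheduled inquiry, and Table 2 states the outcome without it.

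**Conclusion.** The point holds as a risk of under-capture and as a disagreement on scope between the safety section and Table 2. It is not a demonstrated loss of events. It rests on reading the opening sentence of the safety section as the definition of the rating, and on the questionnaire asking what the article says it asks.

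The number of events affected is unknown. It would be tempting to set an upper confidence limit for zero events among the 160 intervention participants against a limit for a few missed events. The documents give no event rate, and any count of missed events would be invented, so no rate should be quoted. The direction is clearer: a filter at capture can only remove events from the list.

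A reader might also infer that the filter distorts a comparison between arms. Table 2 collects safety in the intervention group only, so no such comparison of event counts is planned there. Whether it should be is a separate question.

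The change is worth making because it is inexpensive and serves a stated aim, but it does not affect the primary analysis.

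**What to change.** 1. In the safety section, define the recorded outcome as all adverse events whatever the presumed cause, so that it matches Table 2. Exercise-related events then become a reported subset.
2. Reword the t3/t6 item as an open question on any health event since the last contact. If questionnaires have already gone out, note the date of the change.
3. Have the study physician already named in that section assign relatedness after recording.
4. Add one table of hospital and disability-day data from the insurance database, by arm, as an attribution-free check on the more serious events. This assumes that the extract identifies hospital stays as well as their cost.

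The cost is some rewording, physician time for classification and one table from data already being drawn. The downside is a larger number of unrelated minor events to process.

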### Objectives

Evidence is given for the effectiveness of PA in the prevention and treatment of single chronic NCDs, though the literature reveals knowledge gaps regarding the evidence of the effectiveness of PA in people with multimorbidity [26]. The primary aim of this pragmatic trial is to evaluate whether a comprehensive exercise and lifestyle intervention (*MultiPill-Exercise*) can help people to engage in regular PA at the end of a six-month intervention and after another 12 months in a follow-up. We hypothesize that engagement in regular PA – quantified with the EHIS-PAQ – is superior in the intervention group *MultiPill-Exercise* in comparison to usual health care offers. Secondary aims are related to the effectiveness of the program on generic and disease specific health outcomes and disease prevention, health economic outcomes, individual behavioral determinants as well as program adherence and safety. The feasibility of the implementation of *MultiPill-Exercise* into a regular health care setting is monitored by a continuous quantitative and qualitative process evaluation.

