## Methods

### Study design

The study will be conducted in the context of health service research. The feasibility of the intervention and an exploratory analysis of its effects on health outcomes were tested in a non-controlled pilot study (DRKS00016702). Results have been used to optimize the current study design, for example through putting more emphasis on nutrition, extending supervision time during the study period (24 weeks of supervised machine-based training instead of only 12 weeks) and integrating videos into the exercise sessions at home. The current study is now designed as a multi-site randomized controlled superiority pragmatic trial with two parallel groups. It evaluates the effectiveness, efficiency and safety of the 24-week comprehensive lifestyle intervention *MultiPill-Exercise* in comparison to the regular health care offer of a statutory health insurance company. Participants will be randomized to intervention and control group with an allocation ratio of 1:1. Measurements will be taken at baseline (t0), three months (t3), six months (t6), 12 months (t12) and 18 months (t18). The study was prospectively registered in the German Clinical Trial Register (DRKS00025033) and is documented according to the completed Standard Protocol Items: The recommendations for interventional trials (SPIRIT) checklist [27] and the Pragmatic-Explanatory Continuum Indicator Summary (PRECIS)-2 checklist [28] are available as supplements (Additional files 1 and 2).

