### Outcome measures

All participant-reported outcomes will be assessed using SecuTrial online questionnaires (InterActive Systems Berlin) at baseline and all follow-up time points. All physical performance measurements will be assessed on-site at t0, t6, t12 only (Fig. 3 and Table 2). The assessor team will consist of members of the study team, composed of employees of the university and university hospital, as well as a physician of the University hospital at t0. All assessors will be trained in advance and the examinations will follow the same order and predefined standard operating procedures (SOPs). Demographic data, clinical status (details of relevant history of disease, medical history, medications), history of exercise participation and outcome expectations are assessed in addition to primary and secondary outcomes. All on-site data will be directly entered to the electronic case report form (eCRF) using the software SecuTrial. The software automatically performs plausibility queries when the data is saved. The participants will receive E-Mails prior to the data collection, reminding them of the upcoming data collection.

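### Scheduled adverse event questions stop at t6 and Table 2 lists them for the intervention group only, although exercise to t18 is a primary aim and the t12 exercise test follows in both arms

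*Protocol article*

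**What the plan says.** The section on adverse events and side-effects lists several channels. Exercise specialists record the events they learn of. "Participants are urged to report adverse events or side-effects to their guide or to report them in their training-log". The online questionnaire asks directly, at two points: "Exercise-related adverse events are also retrospectively assessed via the online questionnaire at t3 and t6". Two further channels carry no end date: "All participants can further contact the study physician of the university hospital at any time as outlined in the participant information sheet", and "The standard adverse events and severe adverse event form of clinical trials will be implemented in the SecuTrial database".

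Table 2 describes the safety outcome as "Summarized number and details of adverse events and side-effects according to training log and case report form". Its sources are training logs, the on-site case report form and the self-administered questionnaire. Its sample is the intervention group and its collection points are t3 and t6. The section text names no arm for the questionnaire item, so the restriction to one arm comes from the table.

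Other parts of the article run longer. The primary aim is whether people "engage in regular PA at the end of a six-month intervention and after another 12 months in a follow-up". Under Statistical analysis, t12 and t18 are tested as confirmatory if t6 is significant. On the exercise test, Outcome measures says: "All physical performance measurements will be assessed on-site at t0, t6, t12 only". Table 2 lists that test for both arms, and Physiological outcomes describes it as ergometry in rising stages continued to exhaustion.

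**The concern.** The programme is meant to leave people exercising on their own after supervision ends. Injuries or other events in months 7 to 18 may arise from the very behaviour that the trial would count as its benefit. If nobody is asked about them, benefit is followed to month 18 while solicited harm is followed to month 6.

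The arm restriction matters at least as much. An event count from the intervention group alone has no reference. People with osteoarthritis, obesity or cardiovascular risk will have musculoskeletal and other events whatever they are assigned to, and control participants may also take exercise courses. Without the control count, even the first six months give a description and not a comparison. The Conclusion names safety beside effectiveness and efficiency, and envisages direct transfer of the programme into routine.

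**Working it through.** The article gives no figure for the length of the safety period, and no sample size depends on it. The check sets the schedules side by side.

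**Inputs**

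| Item | Time points | Arms | Where stated |
|---|---|---|---|
| Adverse event item | t3, t6 | Intervention (Table 2) | Safety section; Table 2 |
| Primary outcome | t0, t3, t6, t12, t18 | Both | Table 2 |
| Online questionnaires | t0, t3, t6, t12, t18 | Both | Outcome measures; Table 2 |
| Exercise test | t0, t6, t12 | Both | Outcome measures; Table 2 |
| Programme | 24 weeks, assessed at t6 | Intervention | Study design; Statistical analysis |

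**Follow-up time without a scheduled item**

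- End of follow-up minus last adverse event item: 18 − 6 = 12 months.
- Share of follow-up: 12 / 18 = 0.67.

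**Exercise tests after the last item**

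- Tests at 0, 6 and 12 months; those later than month 6: one of three, at t12.

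**What remains open after t6**

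- Training logs, guides and on-site specialists are tools of the 24-week programme. The article describes no use of them after it.
- Contact with the study physician and the event form have no stated end. Both depend on someone reporting without being asked.
- HOOS/KOOS and pain (participants with osteoarthritis) and back pain severity (all) are collected to t18. Medication is recorded at t12. Insurance data on costs and days of disability run to t18. All of these cover both arms. They may reflect harm, but they are scores and totals, without an event description or a link to exercise.

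**Comparison between arms**

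- Under Table 2, adverse events are counted in one arm, so a risk difference or ratio cannot be formed for any period, including t0 to t6.

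**The case against.** The strongest reply is that the scope is deliberate. Study design speaks of the safety of the 24-week intervention, and the safety section rates exercise-related events of that intervention. The Discussion marks research questions (1) to (4) for short- and long-term evaluation; safety sits in question (5). The window therefore matches the declared question. The article also condenses a fuller protocol, and the participant information sheet it cites is not shown. Long-term activity is a hypothesis, and the authors expect the effect to fall over follow-up. This stands in part: it rules out a contradiction. It does not remove the point, because the article itself fixes the time points and the sample in Table 2.

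Several stronger readings are tempting, and the documents do not support them.

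- A reader might infer that nothing on safety is recorded after t6. Physician contact at any time and the event form speak against that; only solicited collection ends.
- A reader might infer that joint worsening goes unasked. HOOS/KOOS and pain are collected at t12 and t18 in participants with osteoarthritis.
- A reader might see an error in listing the on-site form as a source at t3, when no assessment visit takes place. The footnote to Table 2 says that exercise specialists also provide that form, and they are on site during the programme.
- A reader might use the number of t12 tests as the size of the gap. The test is a study assessment given to both arms, so an event at it says little about the programme. Nor is it unobserved: the ECG is recorded throughout and reasons for stopping are listed.

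**Conclusion.** The point holds as a limit of scope. Scheduled adverse event collection covers 6 of 18 months, omits the t12 exercise test and, by Table 2, covers one arm of two. After t6 the article describes only unprompted reporting and indirect measures. The listed data can support a description of events in the intervention group during the programme. They cannot support a comparison of harms between arms, nor a statement about safety over the period in which t12 and t18 activity is assessed.

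This rests on two readings: that Table 2 is complete for the adverse event item, and that logs and guides end with the 24-week programme, which the article implies but does not say. If the full protocol sets a longer reporting period or asks both arms, Table 2 should be brought into line with it. No sample size or efficacy analysis is affected.

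**What to change.** In Table 2 and in the safety section:

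1. Put the adverse event item to both arms at t3, t6, t12 and t18, in the online questionnaires already sent. Changing the time points without the sample would only give a longer uncontrolled count.
2. Add an adverse event entry to the on-site form at the t0, t6 and t12 test visits, so that events at a test are recorded whether the questionnaire is completed before or after the visit.
3. State the period over which adverse events are collected.
4. Report months 0-6 and 7-18 separately by arm, and list test-related events apart from programme-related ones. Base the comparison on the questionnaire and the visit form. Participant training logs and guides exist in the intervention arm only and would raise its count through closer observation.

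The cost is a few questionnaire items and one form page at contacts that already exist, slight respondent burden, and more event forms to process. At t12 and t18 the recall period would be six months (12 − 6 and 18 − 12) against three at t3 and t6, so minor events in months 7-18 may be under-reported. That is a further reason to show the two periods separately.
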